### 13.4 Evaluation of AEs

The Sponsor expects that AEs are recorded in the medical notes from the point of Informed Consent regardless of whether a participant has yet received a medicinal product. Individual AEs should be evaluated by the investigator. This includes the evaluation of its seriousness, and any relationship between the IMP(s) and/or concomitant therapy and the AE (causality).

#### 13.4.1 Assessment of seriousness

Seriousness is assessed against the criteria in section 13.1.4. This defines whether the event is an AE, SAE or SAR.

#### 13.4.2 Assessment of causality

- Definitely: A causal relationship is clinically/biologically certain. **This is therefore an Adverse Reaction**
- Probable: A causal relationship is clinically / biologically highly plausible and there is a plausible time sequence between onset of the AE and administration of the IMP and there is a reasonable response on withdrawal. **This is therefore an Adverse Reaction.**
- Possible: A causal relationship is clinically / biologically plausible and there is a plausible time sequence between onset of the AE and administration of the IMP. **This is therefore an Adverse Reaction.**
- Unlikely: A causal relation is improbable and another documented cause of the AE is most plausible. **This is therefore an Adverse Event.**
- Unrelated: A causal relationship can be definitely excluded and another documented cause of the AE is most plausible. **This is therefore an Adverse Event.**

Unlikely and Unrelated causalities are considered NOT to be trial drug related.

Definitely, Probable and Possible causalities are considered to be trial drug related.

A pre-existing condition must not be recorded as an AE or reported as an SAE unless the condition worsens during the trial and meets the criteria for reporting or recording in the appropriate section of the CRF.

#### 13.4.3 Clinical assessment of severity

- Mild: The participant is aware of the event or symptom, but the event or symptom is easily tolerated
- Moderate: The participant experiences sufficient discomfort to interfere with or reduce his or her usual level of activity
- Severe: Significant impairment of functioning; the subject is unable to carry out usual activities and / or the participant's life is at risk from the event.

#### 13.4.4 Recording of AEs

AEs should be recorded in the medical notes. ARs and AESI should also be recorded in the appropriate section of the CRF. SAEs and SARs should be reported to the sponsor as detailed in section 13.4.

### **13.5 Reporting SAEs/SARs**

Each PI needs to record all AEs in the medical notes and report all serious AEs to the CI and TURING trial team using the trial specific SAE form within 24 hours of knowledge of the event. However, SAEs related to the underlying disease, as indicated in Section 13.2.4, will be exempt from expedited SAE reporting. These events will be designated as Adverse Events of Special Interest and details will be collected in the CRFs.

The Chief Investigator (CI) is responsible for ensuring the assessment of all SAEs for expectedness and relatedness is completed and the onward notification of all SAEs to the Sponsor immediately but not more than 24 hours of site investigator awareness of the event. The sponsor has to keep detailed records of all SAEs reported to them by the trial team.

The CI is also responsible for prompt reporting of all SAEs findings to the competent authority (e.g. MHRA) of each concerned Member State if they could:

- adversely affect the health of participants,
- impact on the conduct of the trial,
- alter the risk to benefit ratio of the trial,
- alter the competent authority's authorisation to continue the trial in accordance with Directive 2001/20/EC.

The completed SAE form can be faxed or emailed. Details of where to report the SAE's can be found on the TURING SAE form and the front cover of the protocol.

### **13.6 Reporting of SUSARs**

All suspected ARs related to an IMP (the tested IMP and comparators) which occur in the concerned trial, and that are both unexpected and serious (SUSARs) are subject to expedited reporting. Please see Section 13.1.6 for the RSI to be used in this trial.

#### 13.6.1 Who should report and whom to report to?

The Sponsor delegates the responsibility of notification of SUSARs to the CI. The Chief Investigator must report all the relevant safety information previously described, to the:

- Sponsor

- Competent authorities in the concerned member states (e.g. MHRA)
- Ethics Committee in the concerned member states

The CI shall inform all investigators concerned of relevant information about SUSARs that could adversely affect the safety of participants.

### 13.6.2 When to report?

#### 13.6.2.1 Fatal or life-threatening SUSARs

The CI must inform the Sponsor of any fatal SUSAR immediately but within 24 hours of the site investigator awareness of the event. The MHRA and Ethics Committee must be notified as soon as possible but no later than **7 calendar days** after the trial team and Sponsor has first knowledge of the minimum criteria for expedited reporting.

In each case relevant follow-up information should be sought and a report completed as soon as possible. It should be communicated to all parties within an additional **8 calendar days**.

#### 13.6.2.2 Non-fatal and non-life-threatening SUSARs

All other SUSARs and safety issues must be reported to the Sponsor immediately but within 24 hours of the site investigator awareness of the event. The MHRA and Ethics Committee must be notified as soon as possible but no later than **15 calendar days** after first knowledge of the minimum criteria for expedited reporting. Further relevant follow-up information should be given as soon as possible.

### 13.6.3 Minimum criteria for initial expedited reporting of SUSARs

Information on the final description and evaluation of an adverse reaction report may not be available within the required time frames for reporting. For regulatory purposes, initial expedited reports should be submitted within the time limits as soon as the minimum following criteria are met:

- a) a suspected investigational medicinal product
- b) an identifiable participant (e.g. trial participant code number)
- c) an adverse event assessed as serious and unexpected, and for which there is a reasonable suspected causal relationship
- d) an identifiable reporting source

And, when available and applicable:

- a unique clinical trial identification (EudraCT number or in case of non-European Community trials the sponsor's trial protocol code number)
- a unique case identification (i.e. sponsor's case identification number)

#### 13.6.3.1 Follow-up reports of SUSARs

In case of incomplete information at the time of initial reporting, all the appropriate information for an adequate analysis of causality should be actively sought from the reporter or other available sources. Further available relevant information should be reported as follow-up reports.

In certain cases, it may be appropriate to conduct follow-up of the long-term outcome of a particular reaction.

### 13.6.3.2 Format of the SUSAR reports

Electronic reporting is the expected method for expedited reporting of SUSARs to the competent authority. The format and content as defined by the competent authority should be adhered to.

## 13.7 **Pregnancy reporting**

All pregnancies within the trial should be reported to the CI/TURING Trial coordination center and the Sponsor using the relevant Pregnancy Reporting Form within 24 hours of notification. Pregnancies will be reported until trial close.

Pregnancy is not considered an AE unless a negative or consequential outcome is recorded for the mother or child/fetus. If the outcome meets the serious criteria, this would be considered an SAE.

## 14 **EVALUATION OF RESULTS (Definitions and response/evaluation of outcome measures)**

### 14.1 **Definitions of Remission and Relapse**

Primary outcome measure: Time from partial or complete remission (whichever documented first) to relapse as defined below (see appendix 6):

- COMPLETE REMISSION (CR): PCR < 50mg/mmol (only one result required).
- PARTIAL REMISSION (PR): Reduction in Urinary PCR  $\geq$  50% from Day 0 - Start of Protocolised Prednisolone Regimen (SPPR) AND PCR  $\geq$  50mg/mmol and  $\leq$  300mg/mmol on two consecutive results (performed within 14 days of each other). The date of first assessment is the date of partial remission.
- RELAPSE: recurrent NS as defined by albumin < 35 g/l, PCR > 300mg/mmol and an increase in 100% over the nadir value during remission on two consecutive results (performed within 14 days of each other). The date of first assessment is the date of relapse. For patients with an albumin  $\geq$  35g/l prior to relapse, only one PCR result is required (i.e. PCR > 300mg/mmol that has risen by 100% over the nadir value and an albumin < 35g/L).

### 14.2 **Evaluation Procedure**

Remission will be assessed 4 (+/- 1) weekly from Day 0 (SPPR) until week 16. After remission, relapse will be assessed 4 (+/- 1) weekly for 12 weeks and then 3 (+/- 2 weeks) monthly from the date of remission. Additional assessments could be performed if clinically indicated or from the patient self-monitoring of urine protein stick testing results.

## 15 **STORAGE AND ANALYSIS OF SAMPLES**

No samples will be stored as part of TURING. All specimens will be analysed at each participating site. The exception to this will be the urinalysis which will be performed by the

participant in their own homes and the results will be recorded in the urinalysis diary provided.

## 16 STATISTICS

### 16.1 Statistical Methods

#### 16.1.1 Analysis populations

The following populations will be defined for efficacy and safety analyses:

- **Intent-to-treat population (ITT)**  
The ITT population is defined as all patients randomised in the trial, regardless of whether they actually received treatment. The treatment group will be analysed as randomised.
- **Responding patient population**  
Responding patient population is defined as all patients randomised in the trial, received allocated protocol treatment and achieved partial/complete remission. The treatment group will be analysed as randomised.
- **Safety population**  
The safety population comprises all patients randomised and having received at least one dose of trial treatment. The treatment group will be analysed as treated.

#### 16.1.2 Primary assessment of the efficacy of rituximab at trial end

The primary objective of the trial is to assess the effect of rituximab on the time from remission to relapse of NS. The most clinically relevant benefit is to maintain remission as long as possible whilst minimising steroid toxicity, that is, the duration of remission in responding patients.

There is no evidence of difference in the distribution of time to remission between the two arms. The stratified log-rank test stratifying the factors used for randomisation will be used.

Otherwise, the probability-of-being-in-response function (PBRF) will be used as a means of estimating the expected duration of remission (EDoR) across all randomised patients given as the estimated response rate times mean duration of remission for responding patients. The analysis will be based on ITT population.

Briefly, considering a stochastic process in which a patient must start in State 0 (that is at Day 0) and eventually progress to an absorbing state, 2 (progression, death in the absence of progression, treatment failure at week 16, relapse (or died from disease), possibly passing through a transient state 1 (remission). Response and duration of response are assumed to be independent.

[figure not shown]

Summary statistics together with the Kaplan-Meier curves for the duration of remission in responding patients by treatment arm and estimated will also be presented. Detailed statistical analysis methods will be included in the statistical analysis plan.

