### **16.2 Number of Patients to be Enrolled**

The primary outcome measure is time from remission to relapse from partial/complete remission. With 78 patients randomised at a steady rate over a period of 30 months, who subsequently achieved a partial/complete remission, and an additional 24 months follow-up after the last patient randomised (estimated at 54 months after the first patient was enrolled), the trial will have 80% power (two-sided test, significance level of 5%) to show a 50% change in time to relapse from a median value of 9 months in the control arm to 18 months in the research arm, (i.e. a hazard ratio of 0.50). It is expected that the 67 primary outcome measure events required will have occurred at this point. To achieve 85% power (two-sided test, significance level of 5%) requires 76 events. To achieve 90% power (two-sided test, significance level of 5%) requires 89 events. See appendix 5 for sample size output.

With an estimated 75% remission rate, allowing for non-compliance of the order of 5%, a total of approximately 112 ( $112 \times 70\% = 78.4$ ) would be needed. Further allowing for an early drop out (prior to remission assessment) of the order of 5% and withdrawal due to COVID-19 pandemic, approximately a minimum of 130 and up to 150 patients in total will be enrolled.

Although the effect size of  $HR=0.50$  upon which sample size calculations are based appears large, two placebo RCTs of rituximab in children with FR NS have given lower HR at 0.267 (CI 0.135-0.528) and 0.02 (CI 0.01-0.15).

The assumptions used in the sample size estimation will be monitored by the Independent Data Monitoring Committee (IDMC). A sample size re-estimation might be performed if this is recommended by the trial IDMC.

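### Section 16.1.2 lets the trial's own time-to-remission data choose between two different primary analyses, and only one of them is sized

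*Protocol*

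**What the plan says.** Section 8.5.1 gives the primary objective as the effect of rituximab on the time from remission to relapse, and section 16.2 agrees: "The primary outcome measure is time from remission to relapse from partial/complete remission".

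Section 16.1.2 then sets out the primary analysis in two steps. It first asserts that "There is no evidence of difference in the distribution of time to remission between the two arms" and specifies a log-rank test stratified by the randomisation factors. The following paragraph starts with 'Otherwise' and says that the probability-of-being-in-response function (PBRF) "will be used as a means of estimating the expected duration of remission (EDoR) across all randomised patients". EDoR is defined there as the estimated response rate multiplied by the mean duration of remission in responders. A sentence placing the analysis in the ITT population follows. Time to remission, on which the first sentence turns, is itself a secondary outcome in section 8.6.2.

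Section 16.2 and Appendix 5 size the trial for a log-rank test on medians going "from a median value of 9 months in the control arm to 18 months in the research arm" ("i.e. a hazard ratio of 0.50"). They contain no calculation for EDoR.

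**The concern.** No between-arm comparison of time to remission can exist before the trial has data, and 'Otherwise' has no meaning unless the sentence before it is a condition. The sensible reading is that an 'If' has been lost. The observed remission data would then decide which primary analysis is run.

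The two branches estimate different things. The log-rank test concerns how long remission lasts in those who reach it. EDoR also counts how many reach it, so it can favour rituximab when duration is identical in the arms. Because EDoR contains the response rate, it is correlated with the comparison that triggers it, and it is used just when the remission curves have separated, by chance or otherwise. The protocol states no test or threshold for the switch and no control of error across the branches. At stake are the meaning of the primary p-value and the claim that it is a 5% test of the stated objective.

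**Working it through.** **1. The plan's own figures.** Inputs from section 16.2: HR 0.50, two-sided 5%, 1:1 allocation. Schoenfeld: events = 4(z₀.₉₇₅ + z_power)² / (ln HR)², with (ln 0.5)² = 0.4805.

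- 80%: 4 × (1.960 + 0.842)² / 0.4805 gives 66; the plan has 67 ("It is expected that the 67 primary outcome measure events required will have occurred at this point").
- 85%: 75; the plan has 76 ("To achieve 85% power (two-sided test, significance level of 5%) requires 76 events").
- 90%: 88; the plan has 89.

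With uniform accrual over 30 months and closure at 54, P(event) = 1 − [exp(−24λ) − exp(−54λ)] / (30λ). For λ = ln 2/9 this is 0.939, and for λ = ln 2/18 it is 0.765. The mean is 0.852, and 78 × 0.852 = 66.4 events. The sample size therefore reproduces, for the log-rank branch.

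**2. The two-stage rule.** The protocol gives neither the pre-test nor an EDoR test, so these are assumptions:

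- Pre-test: two-sided log-rank on time to remission, at 5, 10 or 20%.
- Not significant: log-rank on remission duration in remitters (simulated unstratified).
- Significant: Wald test on log(response rate × mean duration), with the mean taken either as an exponential estimate or restricted to 20 months.
- Exponential times, 4-weekly remission assessment to week 16, 75% control remission, 9-month control median, response and duration independent (as section 16.1.2 assumes), N = 130 and 150.

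**3. No effect on remission or duration** (20,000 trials per N, Monte Carlo SE about 0.16 points). Ranges run over both EDoR estimators and, for the rule, over pre-test levels of 5 to 20%.

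| N | Log-rank alone | EDoR alone | Two-stage rule |
|---|---|---|---|
| 130 | 5.3% | 5.1–5.3% | 5.8–6.6% |
| 150 | 5.2% | 4.7–5.0% | 5.6–6.4% |

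Once the pre-test is significant at 5%, EDoR rejects in 13 to 20% of trials. The parts add up. For N = 150 with the exponential mean, 0.951 × 0.0515 + 0.049 × 0.132 = 0.0490 + 0.0065 = 5.6%, as simulated. A second simulation, with time in remission to 24 months standing in for EDoR, gave 5.8 to 6.8%.

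**4. Effect on remission, none on duration** (N = 150, HR 1, 6,000 trials each, 5% pre-test).

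| Remission, control v rituximab | Pre-test significant | Two-stage rejection |
|---|---|---|
| 75% v 80% | 13% | 6.4–7.5% |
| 75% v 85% | 41% | 9.0–12.5% |
| 75% v 90% | 80% | 14.9–23.3% |
| 75% v 95% | 99% | 23.0–37.9% |

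At a 20% pre-test level the upper figure for 75% v 85% becomes 13.3%. The second simulation gave 10.6 to 12.4% at 85% and 31 to 32% at 95%. The log-rank test alone stays at 5.1 to 5.6% throughout. The reason is direct: with equal durations the true EDoR ratio at 95% v 75% is 0.95/0.75 = 1.27, while the hazard ratio for relapse is 1.

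**5. Power at HR 0.50, 75% remission in both arms** (4,000 trials each). Log-rank alone: 87.9% (N = 130) and 91.7% (N = 150). EDoR alone: 81.7% and 86.7% with the exponential mean, 51.6% and 57.1% with the restricted mean. Two-stage rule: 80.8 to 87.3% and 84.5 to 91.3%.

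**The case against.** The conditional rule is inferred. As written, the sentence is a statement of fact, and it could be a justification left over from editing. That stands as a caution. It does not rescue the section, because on that reading the protocol asserts a trial result in advance and 'Otherwise' refers to nothing.

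The statistical analysis plan, which is not at hand, may specify the switch. It could add a test and a threshold, but it could not remove a data-driven choice that the protocol fixes without contradicting the protocol.

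The simulated rule is not the protocol's own, since section 16.1.2 presents EDoR as an estimate and states no test for it. That also stands, and it is why the results are ranges. Rejections in the EDoR branch are not errors for EDoR's own question; they are errors for the stated objective.

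The change of population is less explicit than the change of quantity, because the ITT sentence might cover both branches. Even so, a log-rank test of time from remission can use only those who remitted.

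A reader might infer more than the document supports:

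- **That the mean duration cannot be estimated.** Section 16.1.2 does not say how the mean is to be taken and specifies no Kaplan-Meier mean. A parametric mean is estimable under censoring.
- **That doses 1 and 2 precede most remissions.** Sections 10.1.7 and 11.4 allow dose 1 up to week 4 and dose 2 up to four weeks after it, so as late as week 8. Remission is assessed from week 4, and section 9.5.1 foresees remission and relapse before the first dose. No distribution of time to remission is given.
- **That extra remitters on rituximab relapse faster and bias the log-rank test by a known amount.** The protocol gives no such rate. Selection of remitters is a reason for supporting analyses, not a quantified bias.
- **That the pre-test would rarely detect a difference.** At 75% v 85% it is significant in 41% (5% level) to 67% (20% level) of trials in the main simulation, and in about 26% to 53% in the second.

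**Conclusion.** The point holds. Section 16.1.2 does not fix one primary analysis, and on its only coherent reading the observed remission data select it. With no effect of any kind the cost is small: 5.6 to 6.8% instead of about 5%. It would be wrong to describe this as gross inflation. The more serious matter is interpretation. If rituximab changes remission but not duration, a positive primary result becomes likely (roughly 9 to 13% at 75% v 85%, 23 to 38% at 75% v 95%) with no effect on time from remission to relapse.

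The sample size is not at fault, but its power and event counts describe the log-rank branch only. When only duration differs, power under the rule is 0.5 to 7 points below the log-rank test alone and stays above 80% in these simulations. All simulated figures rest on the assumed pre-test level, EDoR estimator and exponential times. The existence of the defect rests only on the wording of section 16.1.2.

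**What to change.** In section 16.1.2, delete the sentence on time to remission and the word 'Otherwise', and name one primary analysis that applies whatever the remission data show. The simplest choice is the stratified log-rank test of time from remission to relapse, because it matches section 8.5.1 and is what section 16.2 and Appendix 5 size. State that it is run in patients who remit, analysed as randomised.

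That test compares patients selected after randomisation, so always report two pre-specified supporting analyses in all randomised patients: PBRF/EDoR time in remission over a stated horizon (24 months from Day 0, the minimum follow-up in section 8.4, is a natural candidate), and the time to treatment failure already listed in section 8.6.2. They help to show whether selection of remitters drives the result. The analysis plan should follow the same wording.

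The cost is a wording amendment and a little extra analysis. No new data or patients are needed, and with one analysis fixed in advance the simulated error returns to about 5%.

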#### *16.1.3 Censoring*

For patients who have achieved partial/complete remission but neither relapsed or died from the disease at the time of the analysis or who are lost to follow up, their data will be censored at the date that they were last known not to have relapsed.

#### *16.1.4 Safety analysis*

The safety analyses will be based on the safety population. All safety parameters will be summarised. Summary tables will be presented for incidence rates (number of patients with at least one incidence) of, AESIs, and SAEs.

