##### 9.5.1 *Withdrawal from protocol treatment*

A participant may withdraw, or be withdrawn, from the trial treatment for the following reasons:

- Participants who do not achieve partial remission by 16 weeks after Day 0 (SPPR). The treating clinician may request unblinding of withdrawn participants if required for safety consideration of future treatment – this unblinding will be performed at local site level only
- Participants who enter the trial and remit and relapse before receiving the first dose of trial IMP. In this case the participant can be withdrawn from the trial and re-screened as a new participant. It is recommended the clinician chooses Regimen 1 steroid taper for this participant when re-entering them into the trial
- Progressed or relapsed disease whilst on therapy
- Unacceptable toxicity
- Participant choice
- Addition of other immunosuppressants for treatment of MCD/FSGS
- Any alterations in the participant's condition which justifies the discontinuation of treatment in the investigator's opinion.
- Failure to adhere to infusion visit schedule. With ongoing consent, patients should remain in the trial and be followed up according to the protocol visit schedules. Samples and data collected up to the time of withdrawal will be included in the data reported for the trial.

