### **10.2 Open Label Phase (OLP)**

Patients randomised to placebo who achieve partial/complete remission by week 16, followed by disease relapse (the primary endpoint event) within 24 months of Day 0 (SPPR) will be invited to participate in the Open Label Phase (OLP) of the trial.

Participants who fail to remit by week 16 will be ineligible for the OLP, as patients who are not steroid responsive are unlikely to respond to rituximab therapy. There is limited data in this group, but a single open label RCT in children whose nephrotic syndrome was unresponsive to steroids and CNIs did not show any benefit of rituximab. Data arising from the OLP will not contribute to either the efficacy or safety assessments in the main phase of the trial but will allow exploratory observational analyses, including a comparison of time in remission combining both standard of care or placebo treatment and rituximab treatment.

Those participants in the control arm who consent to the OLP will receive treatment with the intervention described for the rituximab arm in the main trial – i.e. receive rituximab 1g within 4 weeks of relapse and restarting treatment prednisolone, after 2 weeks (+/-7 days) and, if they continue in remission, after 26 weeks (+/- 2 weeks) of restarting treatment dose prednisolone for relapse. Thus participants will attend 3 additional visits on top of standard care for the rituximab infusions. SAE reviews and concomitant medication reviews will be conducted during these visits.

All participants that enter the OLP will recommence protocolised prednisolone therapy as in the main trial (with the regimen at the discretion of the local investigator).

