#### 11.12 **Final trial visit**

The final trial visit will either be:

- At 16 weeks (+/- 1 week) from Day 0 (SPPR) for participants who have not entered complete or partial remission.
- At relapse (+ up to 2 week) for participants who have previously achieved complete or partial remission by week 16. Participants who have received placebo may then enter the Open Label Phase.
- Taken as the last 3 monthly visit they have had when the trial closes for participants who achieved complete or partial remission and did not relapse
- Please note: Trial participants withdrawn from treatment will require safety reporting (SAR/SUSAR only) for up to 12 months post last IMP dose providing that consent to participate in this trial is ongoing.

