## 12 END OF TRIAL PARTICIPATION

All participants who enter remission will continue in trial follow up until relapse or trial closure when the total number of primary endpoint events have been observed (refer to section 16.2), whichever occurs first. It is anticipated that the end of trial will be approximately 30 months after the last patient recruited.

Once participants have completed their participation in the trial, they will return to normal standard of care.

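### Section 16.1.4 summarises safety as a count of patients with an event, although main-phase follow-up ends at relapse, so a drug that delays relapse is observed for longer and looks worse on events that accrue over time

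*Protocol*

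**What the plan says.** Section 16.1.4 fixes the safety summary: "Summary tables will be presented for incidence rates (number of patients with at least one incidence) of, AESIs, and SAEs". The denominator is the safety population of section 16.1.1: "The safety population comprises all patients randomised and having received at least one dose of trial treatment", analysed as treated. Section 8.6.2 lists SAEs and AESIs, including infection and steroid effects, among the secondary outcomes on which the effect of rituximab is to be evaluated.

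How long a patient is observed is set elsewhere:

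- Section 12: "All participants who enter remission will continue in trial follow up until relapse or trial closure", whichever comes first.
- Section 11.12, final visit for relapsers: "At relapse (+ up to 2 week) for participants who have previously achieved complete or partial remission by week 16".
- Section 11.12, final visit for non-remitters: "At 16 weeks (+/- 1 week) from Day 0 (SPPR) for participants who have not entered complete or partial remission".
- Section 10.2, placebo patients who relapse and go on to open-label rituximab: "Data arising from the OLP will not contribute to either the efficacy or safety assessments in the main phase of the trial".
- Section 11.12, the only continuation: "Trial participants withdrawn from treatment will require safety reporting (SAR/SUSAR only) for up to 12 months post last IMP dose". Section 9.5.1 lists "Progressed or relapsed disease whilst on therapy" among the reasons for treatment withdrawal, so this can apply to early relapsers.

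**The concern.** For AESIs and unrelated SAEs, the length of observation depends on the primary outcome. A patient who stays in remission can contribute events for years. One who relapses at month 6 stops contributing them then. If the treatment works, the rituximab arm has more time in which to record a first infection, malignancy, low IgG or steroid complication. A proportion of patients with an event then differs between arms even when the risk per unit time is the same.

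At stake is the benefit-risk reading of a named secondary outcome. An effective drug would look more harmful, and a real safety gain could be hidden. Calling the count an incidence rate invites the reader to believe that time has been allowed for.

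**Working it through.** **Inputs from the protocol.** Median time from remission to relapse 9 and 18 months, HR 0.50; 75% remission; uniform accrual over 30 months; 24 months of follow-up after the last patient (section 16.2). Section 16.5 instead ends the trial at 30 months after the last patient or at 76 events, whichever is later, so 24 and 30 months were both run. Non-remitters leave at week 16, about 3.7 months.

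**Assumptions not in the protocol.** Exponential relapse; equal remission rates by arm; remission 2 months after Day 0 (range 1 to 3.7); the same adverse event hazard in both arms, at the values shown.

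**Reproducing the design.** Schoenfeld: 4(1.96 + 0.842)²/(ln 0.5)² = 65.3, so 66 events against 67 stated. With monthly relapse hazards λ = ln 2/9 = 0.0770 and ln 2/18 = 0.0385, and closure uniform on 24 to 54 months, the relapse probabilities are 0.939 and 0.765 (mean 0.852). From 78 remitters, 78 × 0.852 = 66.4 events. The relapse model therefore matches the plan's own.

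**Observation time, 24-month closure.** For a remitter the mean is t₀ + (1/λ)(1 − A), where t₀ is the time of remission and A is the average of exp(−λ(c − t₀)) over closure times c.

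- Placebo: 2 + 12.98 × (1 − 0.0716) = 14.1 months.
- Rituximab: 2 + 25.97 × (1 − 0.2542) = 21.4 months.
- All treated, placebo: 0.75 × 14.05 + 0.25 × 3.7 = 11.5 months.
- All treated, rituximab: 0.75 × 21.37 + 0.25 × 3.7 = 17.0 months. Ratio 1.48.

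With closure at 30 months: 11.7 against 18.0 months, ratio 1.53. Over remission at 1 to 3.7 months and both closures, the ratio is 1.42 to 1.58.

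**Crude proportions with an identical constant hazard in both arms.** For a remitter with event hazard μ, the probability of at least one event is 1 − e^(−μt₀) + e^(−μt₀) · μ/(μ + λ) · (1 − B), where B is the average of exp(−(μ + λ)(c − t₀)). At 0.3 per year (μ = 0.025 per month) this gives 0.274 and 0.382. A non-remitter has 1 − e^(−0.0925) = 0.088. All treated: 0.75 × 0.274 + 0.25 × 0.088 = 22.8% on placebo, and 0.75 × 0.382 + 0.25 × 0.088 = 30.8% on rituximab.

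| Hazard per year (remission at 2 months) | Closure 24 months: placebo, rituximab, ratio | Closure 30 months: placebo, rituximab, ratio |
|---|---|---|
| 0.1 | 8.8%, 12.6%, 1.43 | 9.0%, 13.2%, 1.48 |
| 0.3 | 22.8%, 30.8%, 1.35 | 23.0%, 31.8%, 1.38 |
| 0.5 | 33.3%, 43.1%, 1.29 | 33.6%, 44.0%, 1.31 |
| 0.6 to month 6, then 0.15 | 27.3%, 32.1%, 1.17 | 27.5%, 32.7%, 1.19 |
| 0.9 to month 6, then 0.1 | 34.2%, 37.7%, 1.10 | 34.3%, 38.1%, 1.11 |

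Under a constant hazard, equal crude proportions would need a true rate ratio of about 0.67: one third fewer events per unit time would look neutral.

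**Dependence on the effect.** With closure at 24 months and a constant 0.2 per year, the crude ratio is 1.65 at HR 0.3, 1.39 at 0.5, 1.20 at 0.7, 1.09 at 0.85 and 1.00 at 1.

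**Would one overall person-year rate cure it?** Only under a constant hazard. In the two declining-hazard rows, with identical arms, total events per 100 patient-years are 34.7 against 28.8 (ratio 0.83) and 44.9 against 34.6 (0.77) with closure at 24 months; the ratios are 0.82 and 0.75 at 30 months. Rituximab looks safer because its extra time is low-risk time. Split at month 6, the rates agree exactly within each period.

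**Does a common early window help?** To month 6, a remitter is observed on average 2 + (1 − e^(−0.308))/0.0770 = 5.44 months on placebo and 2 + (1 − e^(−0.154))/0.0385 = 5.71 on rituximab. Over all treated this is 5.01 and 5.21 months, ratio 1.04 instead of about 1.5.

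**The case against.** The strongest reply is that 16.1.4 promises only descriptive tables, states no test or effect measure, and that detailed methods go to the analysis plan. Person-time methods could well appear there, and their absence here is no fault. That stands. What remains is that the protocol itself states a measure, calls it a rate, and defines it as a count. An analysis plan that adds true rates would then use the same term for something else.

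A reader might infer that all safety reporting stops at relapse. It does not: SAR/SUSAR reporting can continue for participants withdrawn from treatment. Sections 13.2 and 13.3.3 also speak of monitoring special-interest events throughout the trial, and section 9.5.1 keeps treatment-withdrawn patients in follow-up. But section 11.12 makes relapse the final visit and section 12 ends follow-up there. The continuation covers neither non-serious AESIs nor unrelated SAEs. Even if every relapser were covered to 13.5 or 18 months, the observation ratio in remitters would still be 1.32 or 1.22 for the events covered.

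A reader might also take 1.3 to 1.5 as the general size. That needs a constant hazard, whereas the protocol's schedule points to early risk: high-dose prednisolone for up to 16 weeks, CNI withdrawal by week 12, and infusions early and at week 26. Infusion and hypersensitivity reactions cluster at dosing and are little affected. Admissions for fluid overload, hypovolaemia or thromboembolism are tied to active nephrosis and could move the counts the other way.

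**Conclusion.** The point holds for AESIs and SAEs that accrue over time. If rituximab delays relapse as assumed, its arm is observed about 1.5 times as long. With identical true risk, the planned proportions then favour placebo by a ratio of about 1.3 to 1.5 under a constant hazard of 0.1 to 0.5 per year, or about 1.1 to 1.2 if risk is concentrated in the first 6 months. The protocol gives no event rate or hazard shape for this population, so both are assumptions. The distortion vanishes if relapse is not delayed.

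Two stronger conclusions are not supported. The protocol does not plan a biased safety test: with 65 to 75 patients per arm and constant rates of 5 to 100 per 100 patient-years, a false difference would reach nominal two-sided 5% significance about 7% to 29% of the time, so the harm is mainly a misleading table. Nor is the remedy simply to divide by person-years, which can reverse the bias. The primary analysis, sample size and data collection are untouched. This should be fixed before the analysis, but it does not threaten the trial's main result.

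**What to change.** In section 16.1.4:

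1. Stop calling the number of patients with an event an incidence rate.
2. Compare arms by time to first AESI and first SAE, with observation ending at relapse, week-16 exit or closure. State that this assumes leaving at relapse is unrelated to the later risk of the event.
3. Give cumulative incidence at common early times, week 16 and week 26, where follow-up is nearly equal. An estimate over the whole trial with relapse as a competing event would bring back the dependence on relapse and should not lead.
4. In support, show person-time by arm and events per 100 patient-years split by period, for example to week 26 and after.
5. Keep the crude counts as description. Report SAR/SUSARs arising after relapse separately.

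The cost is slightly more analysis and a short change of wording. Event dates and follow-up dates are already collected, so no new visits or data are needed.
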